### Statistical analysis plan

Statistical reporting will follow CONSORT standards [57]. Missing data will be inspected and handled via full information maximum likelihood (FIML) or multiple imputations (MI) as appropriate. The primary analyses will be intention-to-treat (ITT) analyses [69] (i.e. all participants will be included in the analyses according to their randomised allocation) and based on complete case outcome data. A full, detailed analysis plan, including plans for any interim analysis, subgroup analysis, and sensitivity analysis of the primary outcomes, will be prepared and finalised before the analysis. The primary outcome is change in rumination (RRS) from baseline to 6 weeks follow-up. Our analysis will be an Analysis of Covariance (or equivalent regression or linear mixed model) for the primary and secondary endpoints, with baseline scores as the covariate. Models will be fitted using generalized linear mixed models equivalent to ANCOVA regression models.

As a secondary analysis, sensitivity analyses will compare results of imputed models to primary analysis of complete case ITT models.

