### Randomisation, intervention delivery and masking

Participants will be randomised (in a 1:1 ratio) to the two intervention arms. Randomisation will be conducted independently using pre-generated computerised allocations. To promote balance across key participant characteristics across intervention arms, randomisation will be stratified according to gender (male, female, non-binary) and level of worry and rumination (higher, moderate). Prior studies found that individuals scoring in the worst quartile on measures of EC (e.g., rumination, appraisals, interpersonal vulnerabilities) have elevated risk for subsequent anxiety and depression [66]. Elevated levels of RNT have previously been identified for individuals scoring in the worst quartile (at or above 75th percentile) on at least one measure of worry (PSWQ) and rumination (RRS) and in the top tercile on the other measure (at or above the 66th percentile) [53]. We therefore wanted to stratify participants self-identifying as worriers into those who met this threshold criteria (higher RNT group), and those who did not meet this criteria (moderate RNT group, i.e., at least one measure scoring between 50th and 75th percentile). Consenting participants in the treatment group will then be signed up to use the RNT focused variant of the app by members of the research team not involved in assessment. The participant’s email address is used to provide them access to the app.

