#### Sample size

The sample size was calculated based on an estimated minimum clinically important difference (MCID) for the primary outcome of RRS. Prior studies using the RRS indicated a standard deviation (SD) of 8 as the most conservative estimate for a normative population in the target age group (SD = 7.58–8.51) [53]. Combining consensus from experts in rumination, with one recommended approach to identifying a MCID as being half of the SD for the respective index [67], a proposed MCID for the RRS is a reduction of 4 points. Using these values for 90% power, with an alpha of 0.05, an online power calculator for continuous outcome superiority trials [68]^1^ indicated that 85 participants per group (170 in total) are required. Allowing for a 20% follow-up attrition rate, the estimated total sample size required would be 204 participants (102 per group).

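### Randomisation is stratified by gender and RNT level, but the stated ANCOVA names only baseline scores; if the strata are prognostic, the reported standard error is slightly too large

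*Protocol article*

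**What the plan says.** In the protocol article, the section Randomisation, intervention delivery and masking states that "randomisation will be stratified according to gender (male, female, non-binary) and level of worry and rumination (higher, moderate"), which makes six strata. The higher RNT group is defined by the worst quartile on "at least one measure of worry (PSWQ) and rumination (RRS) and in the top tercile on the other measure", so this stratum is a function of baseline RRS and baseline PSWQ together.

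The section Statistical analysis plan describes, for primary and secondary endpoints alike, an ANCOVA or an equivalent regression or mixed model, "with baseline scores as the covariate". Neither gender nor RNT level appears there, and no other section adds them to the model. The same section says that a full, detailed analysis plan "will be prepared and finalised before the analysis". That plan is not shown.

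**The concern.** Stratified allocation forces the arms to be nearly balanced on the strata, which removes between-stratum variation from the treatment estimate. A model without the strata leaves that variation in its residual. To the extent that the strata predict outcome beyond the covariates already included, the reported standard error then exceeds the real variability of the estimate: intervals are a little wide and the test a little conservative.

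The baseline score does not make the strata redundant:

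- Gender is not a score and is not captured by one.
- For RRS, the RNT stratum overlaps with the covariate but also depends on PSWQ. For PSWQ as an outcome the reverse holds.
- For PHQ-9, GAD-7 and WEMWBS, the RNT stratum is not built from the outcome's own baseline at all, yet the same model is stated for these endpoints.

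**Working it through.** **The plan's own figure.** The Sample size section "indicated a standard deviation (SD) of 8 as the most conservative estimate" and says that "a proposed MCID for the RRS is a reduction of 4 points", with 90% power and alpha 0.05. Taken as two-sided:

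n per arm = 2 × (1.960 + 1.282)² × 8² / 4² = 84.1, rounded up to 85, or 170 in total. Power at 85 per arm is 90.3%.

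The stated 85 per group is reproduced. It uses no covariate, so the planned power does not depend on whether the strata are in the model.

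**Cost and gain by formula.** With 170 evaluable, the baseline-only model has 170 - 3 = 167 residual degrees of freedom. Adding gender (2 terms) and RNT stratum (1 term) leaves 164. If the three terms explain a share R² of the remaining variance in the sample, then, with arms balanced within strata,

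SE ratio = √[(1 - R²) × 167/164].

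| R² | SE ratio |
|---|---|
| 0 | 1.009 |
| 1% | 1.004 |
| 2% | 0.999 |
| 5% | 0.984 |
| 10% | 0.957 |

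The break-even is R² = 3/167 = 1.8%. Three irrelevant terms absorb that share by chance on average, so +0.9% is close to a worst case.

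**Simulation for the RRS.** There were 3,000 trials per row, with 85 per arm and outcome SD 8. The following are assumptions that the article does not give: permuted blocks of 4 within the six strata; gender mix 22/73/5%; correlation 0.5 between baseline RRS and PSWQ; and the standardised effects on 6-week RRS in the first column. Baseline scores were drawn from an unselected normal population, without the eligibility cut-offs. The standard errors (SE), empirical SDs and type I error come from runs with no treatment effect; power comes from runs with a 4-point effect. Arrows run from baseline-only to baseline plus strata.

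| RRS / PSWQ / gender effect | Mean model SE | Change | Empirical SD | Type I error | Power, 4 points |
|---|---|---|---|---|---|
| 0.5 / 0 / 0 | 1.064 → 1.066 | +0.2% | 1.050 → 1.054 | 4.4% → 4.5% | 96.7% → 96.4% |
| 0.5 / 0 / 0.2 | 1.063 → 1.059 | -0.3% | 1.068 → 1.069 | 4.9% → 4.9% | 96.4% → 96.6% |
| 0.5 / 0 / 0.4 | 1.064 → 1.046 | -1.7% | 1.029 → 1.029 | 4.2% → 5.0% | 96.5% → 96.5% |
| 0.5 / 0.15 / 0.2 | 1.003 → 0.998 | -0.5% | 1.000 → 1.002 | 5.0% → 5.1% | 97.6% → 97.7% |
| 0.5 / 0.15 / 0.4 | 1.004 → 0.983 | -2.0% | 0.964 → 0.963 | 4.0% → 4.3% | 97.9% → 98.0% |
| 0.4 / 0.3 / 0.5 | 1.027 → 0.988 | -3.8% | 0.996 → 0.991 | 4.1% → 4.9% | 97.4% → 98.0% |

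Monte Carlo error is about 1/√(2 × 3000) = 1.3% for an empirical SD and √(0.05 × 0.95/3000) = 0.4 percentage points for type I error. Small differences in those columns mean little. The change in mean model SE is the steadier measure.

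The reported SE falls as the strata become more prognostic, while the empirical SD stays within 0.5% between the two models in every row. Power moves by -0.3 to +0.6 percentage points.

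**The case against.** The strongest objection is that the article is a condensed account, leaves the model form partly open and defers to a detailed plan that may add the strata. The plural in baseline scores is also ambiguous. This stands to the extent that nothing says the strata will be excluded. It does not remove the point: the article does state the covariate for both sets of endpoints, the statement does not match the randomisation, and no reading of baseline scores includes gender.

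The second objection is that the effect is conditional. The article gives no evidence that gender or RNT level predicts 6-week outcome once the outcome's own baseline is in the model. It does cite prior work linking worst-quartile scores to later anxiety and depression, but that is not the same claim. This objection stands, and the conclusion has to be worded conditionally.

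A reader might infer three stronger things, none of which is supported:

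- **That the standard errors are certainly too large.** If the strata are not prognostic, adding them raises the SE slightly.
- **That real precision or power is being given up.** Stratified allocation already delivers the balance, so mainly the reported SE changes.
- **That the overstatement is substantial.** A reduction of 6.0% in the mean SE (0.972 to 0.914) can be simulated with 204 participants and residual SD 6.5. It needs a 6-point gender gap remaining after baseline adjustment, which is 0.75 of the stated SD of 8 and exceeds the 4-point minimum important difference.

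**Conclusion.** The mismatch is real and minor. If the strata are prognostic beyond the outcome's own baseline, the model as stated will report a standard error that is somewhat too large and a test that is slightly conservative. For the RRS with 170 evaluable, adding the strata changes the reported SE by about +0.2% to -3.8% and power for 4 points by less than 1 percentage point. There is no bias and no type I error inflation: the baseline-only model rejected in 4.0% to 5.0% of null trials. It is unlikely that any conclusion of the trial would change.

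The range rests on the assumed correlations, gender effects, gender mix and block size. The secondary outcomes were not simulated. For PHQ-9, GAD-7 and WEMWBS the overlap argument is weaker, because the RNT stratum is not derived from their own baselines.

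**What to change.** Specify the primary and secondary models, before the analysis, as: outcome ~ arm + baseline value of that outcome + gender + RNT stratum, with both factors as used at randomisation. Add a prespecified pooling rule in case the non-binary stratum is too sparse to estimate. This also settles what baseline scores means.

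The cost is one line of text and about 3 of 167 residual degrees of freedom, with an SE increase of under 1% if the strata are not prognostic. Both factors are known before randomisation, so no new data are needed.

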### Organization, quality assurance and data management

Research data will be automatically collected in a pseudonymised manner through an electronic data capture system delivered from the website through to the central study database. In the first instance all participants will be directed to the website to provide their data. All data will be kept securely and confidentially and only accessed by members of the research team.

### Trial status

The Trial was registered in ClinicalTrials.gov. Number of identification: NCT04950257 (www.clinicaltrials.gov).. Recruitment commenced in May 2021.

## Discussion

Improving the mental health of young people has recently been identified as a global health priority [4, 70]. This includes both the prevention of poor mental health, such as the onset of anxiety and depression, and the promotion of increased well-being. In order to reach large numbers of young people, effective approaches to improve prevention and well-being promotion need to be widely accessible and highly scalable. As the majority of young people use mobile devices, one potential approach to delivering such an intervention is through the use of mobile apps (m-health).

The identification of effective prevention interventions can be achieved by developing interventions that target known mechanisms for vulnerability to mental health disorders and evaluating whether they effectively reduce this vulnerability factor using prevention mechanism trials [55]. This trial is one such prevention mechanism trial and will thus test as proof-of-concept whether the self-help app is effective at reducing RNT (worry and rumination), which are proven risk factors for multiple mental health problems. If the self-help app is effective at reducing worry and rumination, this will suggest that the intervention may be of value for long-term prevention and is worthy of further longer-term investigation.

Because this intervention is based on a smartphone app and is entirely self-help, without requiring support or therapist time, it has the ability to be scaled up to be widely available as a public health intervention. This work may thus contribute to large-scale effective preventions for young people, i.e., massive open online interventions (MOOI) [71], and has the potential to be hugely beneficial.

## Data Availability

Anonymised datasets arising from this trial will be made available after the primary outcomes are published to researchers and other groups via request to a data committee within the Consortium via the University of Exeter’s open access data system Open Research Exeter (ORE). The results will additionally be updated on ClinicalTrials.gov Identifier: NCT04950257. The ECoWeB consortium plans to communicate trial results through peer-reviewed open access publications and direct reports to TSC, sponsor, and participants.

## Abbreviations

ANCOVA: Analysis of Covariance
BIT: Behavioural Intervention Technology
CBT: Cognitive Behavioural Therapy
CPM: Component Proess Model of Emotion
CONSORT: Consolidated Standards of Reporting Trials
DMC: Data Monitoring Committee
EC: Emotional Competence
ECoWeB: Emotional Competence for Well-Being in Young Adults
FIML: full information maximum liklihood
GAD-7: Generalized Anxiety Disorder-7
ITT: intention-to-treat
MCID: minimum clinically important difference
MI: multiple imputations
MOOI: massive open online interventions
PHQ-9: Patient Health Questionnaire
PSWQ: Penn State Worry Questionnaire
RCT: randomised controlled trial
RNT: Repetetive Negative Thinking
RRS: Ruminative Response Scale
SD: Standard Deviation
TSC: Trial Steering Committee
UK: United Kingdom
WEMWBS: Warwick-Endinburgh Mental Well Being Scale
